#### Inclusion and exclusion criteria

Inclusion criteria for participation are: current DSM-5 diagnosis of PTSD; receiving PTSD treatment of at least three sessions at one of the participating Arkin Mental Health departments; and having parenting responsibilities for at least one child aged 4–17 (biological or legal relationship not required). Exclusion criteria are: urgent care needs which impede participation or (imminent) crisis (e.g., current psychosis, substance detoxification, active suicidality); no contact with children; receiving another parenting intervention during the participation period; severe psychological problems or intellectual disability in children (diagnosis of oppositional-defiant disorder, conduct disorder, current psychosis, personality disorder, or IQ < 50); and inability to participate in the intervention and/or assessments (e.g., unable to speak or read Dutch).

These criteria are similar to inclusion criteria for the original KopOpOuders Self-Help-intervention, but have been adapted to the goals and population of the current study (i.e., the first two inclusion criteria replace the more general KopOpOuders Self-Help criterion that parents should have some form of mental or substance abuse disorder) and on evaluation of KopOpOuders Self-Help (i.e., the age range of children was narrowed from 1 to 17 to 4–17, because intervention content is less applicable to younger children [38]. If a participant’s situation changes so that urgent care needs or severe family problems warranting intervention arise during study participation, their participation will be discontinued and their main practitioner will ensure they receive the appropriate support.

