#### Expansion to blended care

The three minimal contact moments were replaced by three 90-minute in-person sessions with a preventive mental health professional. To uphold the emphasis on parental autonomy and self-direction while instituting more extensive contact with a professional, the role of the professional is that of ‘facilitator’ rather than ‘leader’. All professionals receive a 12-hour training, and sessions are carried out according to a manual to ensure consistency. Whereas the content of the online modules remains largely the same as in the original KopOpOuders Self-Help-intervention (and thus applicable to a wide range of mental health and addiction problems), the in-person sessions have a more in-depth and PTSD-specific focus. In the sessions, parents receive psychoeducation about PTSD and parenting, are encouraged to ask for individualized guidance, and get the opportunity to practice newly learned skills. In-person sessions are carried out one-on-one, but parents are encouraged to bring a partner or other significant person in the final session.

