#### Inclusion, pretest, and randomization

The participant meets with a research team member for an inclusion, pretest, and randomization appointment, either in person at the treatment location or by video call. The participant receives and reads the participant information letter beforehand. First, the researcher answers any questions the participant might still have. The participant then signs the informed consent form. Next, the participant completes the pretest questionnaires online on a computer or tablet. The researcher remains in the room (or on the video call) to provide help if needed. If a participant has multiple children aged 4–17, they are instructed to report on the child they have most concerns about (the ‘index child’).

Participants who agree to take part in the EMA-component then receive instruction on how to install and use the EMA app, Ethica Data [81], on their smartphone. If a participant does not have a smartphone, they can borrow one from the research team. Participants also receive a written copy of the instruction including tips for troubleshooting the app if needed.

Finally, the participant is randomized to the intervention or control condition using the Castor Electronic Data Capture randomization module [80]. Participants are directly informed of their outcome. If a participant in randomized to the intervention condition does not have a computer, laptop or tablet at home, they will be instructed on how they can use computer rooms at their treatment location to complete the online modules.

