### Analysis

Primary analyses will be conducted on the entire randomized sample (i.e., intention to treat). Extra analyses for comparison will be conducted on the per protocol/treatment completers sample. Participants in the intervention condition who have completed at least six out of eight intervention modules/sessions will be characterized as treatment completers. Participants who fail to complete the intervention, but do not choose to drop out of the study, will complete the posttest and follow-up assessments as normal. Hypothesis testing will be two-sided with an alpha level of .05. Missing data will be handled using multiple imputation (R package MICE or equivalent).

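### The discontinuation rule for urgent care needs or severe family problems appears to end data collection as well as the intervention, and does not fit the follow-up promised elsewhere

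*Protocol article*

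**What the plan says.** All references are to the protocol article.

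- **Inclusion and exclusion criteria.** The rule covers any participant. It is triggered by urgent care needs, and likewise if "severe family problems warranting intervention arise during study participation, their participation will be discontinued". The main practitioner then arranges suitable support. The sentence does not limit the rule to the intervention and does not say whether questionnaires continue.
- **Inclusion, pretest, and randomization.** "The participant meets with a research team member for an inclusion, pretest, and randomization appointment". Randomisation therefore happens at the pretest visit, and anything that arises later is a post-randomisation event.
- **Week 10: posttest and Week 22: follow-up.** Both sections have a research assistant contact every participant to arrange the assessment. Neither makes an exception.
- **Analysis.** On the analysis set: "Primary analyses will be conducted on the entire randomized sample (i.e., intention to treat"). On follow-up, of those who stop the intervention early, the ones who "do not choose to drop out of the study, will complete the posttest and follow-up assessments as normal". On gaps in the data: "Missing data will be handled using multiple imputation (R package MICE or equivalent").
- **Expansion to blended care.** The intervention arm alone receives "three 90-minute in-person sessions with a preventive mental health professional".

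**The concern.** A severe family problem arising during the trial is close to a poor value of what the trial measures: parenting behaviour (APQ), parenting stress (PSI) and child problems (SDQ-P). If such an event ends questionnaire collection, outcomes go missing for a reason tied to the outcomes themselves. Standard multiple imputation assumes that observed data explain the missingness. Here a deterioration after pretest may be the cause, and the pretest cannot fully predict it.

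Two consequences follow. If such withdrawals are more frequent in one arm than in the other, the estimated effect is biased. If they are equally frequent, precision is still lost. In both cases the loss is avoidable, and an analysis plan written later cannot repair it, because values never collected cannot be recovered.

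**Working it through.** **1. Does the rule end data collection?** The text does not say so outright. Three features point that way.

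- It applies to all participants. Controls have no study intervention to stop, and usual treatment continues for everyone (Week 1–9). For a control, only the assessments are left to discontinue.
- The article uses the word participation to run through the last questionnaire. Study design offers controls the online modules once their participation is over, and Week 22 places that offer after the follow-up questionnaires.
- The exclusion criteria themselves speak of being unable to take part in the intervention, the assessments or both, so participation covers both.

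**2. Side by side with the follow-up text.**

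| Section | Who is assessed after baseline |
|---|---|
| Week 10, Week 22 | everyone |
| Analysis | intervention non-completers, unless they choose to leave |
| Inclusion and exclusion criteria | apparently not those discontinued for urgent needs or severe family problems |

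The third group did not choose to leave. No section says which rule prevails for them.

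**3. The plan's own sample size.** Inputs (Sample size; Analysis; Study design): d = 0.55, power 0.80, two-sided alpha .05, ratio 1:1, 25% dropout. The two-sided t-test gives 52.87, so 53 per arm (power 0.801). 53/0.75 = 70.7, so 71 per arm and N = 142. The stated figures reproduce and the point leaves them unchanged.

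**4. Possible size of bias.** The documents give no rate for this rule, so everything in this step is assumption. A large-sample simulation (1,000,000 per scenario) used a pretest–posttest correlation r of 0.5 or 0.7 and a true d of 0 or 0.55. Withdrawal was either exactly the worst tail of the posttest outcome within each arm, or moderately related to it (latent correlation 0.5). The analysis regressed observed posttest on arm and pretest, standing in for imputation from the pretest. Positive values favour the intervention.

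| Withdrawn, intervention v control | Approx. people of 71 | Bias in d |
|---|---|---|
| 5% v 5%, 10% v 10% | 4 v 4, 7 v 7 | 0.005 or less in absolute value |
| 10% v 5% | 7 v 4 | +0.02 to +0.07 |
| 5% v 10% | 4 v 7 | −0.02 to −0.07 |
| 10% v 2% | 7 v 1 | +0.04 to +0.12 |
| 2% v 10% | 1 v 7 | −0.04 to −0.12 |

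The last row was checked separately, at a true d of 0.55. It mirrors the row above, because the withdrawal rule acts within each arm and swapping the rates swaps the sign.

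Hand check of one cell (10% v 5%, worst tail, r = 0.5). With a fraction p removed from the lower tail at normal quantile z, the mean of the rest rises by φ(z)/(1−p). This is 0.195 at p = 0.10 and 0.109 at p = 0.05, a difference of 0.086. The pretest means differ by 0.5 × 0.086 = 0.043. The fitted slope after truncation is 0.41. Bias = 0.086 − 0.41 × 0.043 = 0.068, which agrees with the top of that row.

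Relative to the planned effect, 0.02/0.55 = 4% and 0.12/0.55 = 22%.

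**5. Precision.** If such losses came on top of the 25% dropout, 71 × 0.75 × 0.95 = 50.6 per arm (power 0.78), and 71 × 0.75 × 0.90 = 47.9 per arm (power 0.76). Whether they would be additional is unknown.

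**The case against.** The strongest reply is that this is a gap in a condensed article. No sentence says that posttest and follow-up stop, and the full protocol may settle it. The reading is indeed an inference. It remains the natural one, though, because the rule as printed covers controls and because the article uses participation to include follow-up. The question is what a printed rule means beside other printed rules, which is more than a missing detail.

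A reader might infer more than the documents support:

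- **That intention to treat is contradicted.** It is not, formally. The Analysis section keeps everyone randomised in the analysis set and imputes missing values. What is lost is the observed outcome, and with it the follow-up of everyone randomised.
- **That the worst outcomes are removed.** This is plausible but not shown. The triggers are care needs and family problems, not questionnaire scores, and the article's examples of urgent needs or crisis include psychosis, detoxification and suicidality in the parent.
- **That the bias favours the intervention.** The three sessions could bring more problems to light in that arm. But every participant also has a treating practitioner, and an effective intervention could leave more severe problems among controls. The sign is unknown.
- **That harm would be hidden.** Safety reporting and monitoring has adverse events reported separately to the primary investigator. At most, deterioration may be under-represented in the outcome data.
- **That the 25% dropout allowance is used up.** It rests on earlier experience with intervention studies in adults with PTSD, which may already include such withdrawals.

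Pretest adjustment and imputation would also recover part of the loss. The simulated range already allows for the pretest.

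**Conclusion.** The point stands as an unreconciled rule with a modest, uncertain effect. As worded, discontinuation appears to end study participation in both arms after randomisation, which does not fit the Week 10, Week 22 and Analysis sections. The resulting missing values are probably related to the outcomes, and imputation from observed data may not repair them.

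On assumed rates of 2% to 10% per arm, the bias in d is about zero when the arms are equal, and about 0.02 to 0.12 in either direction when they are not. It rests on the assumed rates, the assumed link between withdrawal and outcome, and r of 0.5 to 0.7. The documents supply none of these. Whether the clinical rule itself is right is not judged here.

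**What to change.** Reconcile the sentence in Inclusion and exclusion criteria with Week 10, Week 22 and Analysis by separating the end of the intervention from the end of data collection.

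- Leave the care decision with the practitioner as it stands.
- State that these participants stay in the randomised sample and are still invited to the posttest and follow-up questionnaires, unless they withdraw consent or the practitioner advises against contact.
- Record the date and reason of discontinuation and report both by arm, so that readers can see whether the rates differ.

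The cost is about one sentence of protocol text and a reason code; N = 142 does not change. The downside is a few extra questionnaire contacts with families in difficulty, some of whom will decline, so some values will still be missing.

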#### Recruitment

Participants will be recruited among clients of the abovementioned Arkin Mental Health Care departments. Practitioners will ask clients who meet inclusion criteria whether they agree to be approached for this study. Furthermore, continuous recruitment will take place at client intake. Part of the standard intake procedure is the ‘Child Check’, in which the client is asked whether they have parenting responsibilities, how old their children are, and whether their mental health problems affect their children. If during the Child Check a client who will receive PTSD treatment reports having children aged 4–17, they will be asked whether they agree to be approached for the study. Recruitment flyers and posters with contact information of the research team will also be placed in waiting rooms.

### Procedure

#### Pre-inclusion

When a client consents to being approached after receiving information from their practitioner, a research team member will call them to provide information about the study objectives and procedure and answer questions. If the client is interested in participation, the research team member will screen them for inclusion and exclusion criteria and record the result in a screening log.

The start of trauma therapy can bring about temporarily heightened emotional strain and risk of deregulation. During this period, there is a somewhat higher risk of exceeding the window of tolerance resulting in hyperarousal (e.g., increased intrusive symptoms) and/or hypoarousal (e.g., increased avoidance). In hyper- and hypoarousal states, affect tolerance and learning ability are temporarily decreased [85]. To prevent adverse emotional reactions and dropout, participants can therefore only start participating in the study after at least three sessions of PTSD treatment. Starting sooner is only possible if both client and practitioner consider this suitable and beneficial.

#### Inclusion, pretest, and randomization

The participant meets with a research team member for an inclusion, pretest, and randomization appointment, either in person at the treatment location or by video call. The participant receives and reads the participant information letter beforehand. First, the researcher answers any questions the participant might still have. The participant then signs the informed consent form. Next, the participant completes the pretest questionnaires online on a computer or tablet. The researcher remains in the room (or on the video call) to provide help if needed. If a participant has multiple children aged 4–17, they are instructed to report on the child they have most concerns about (the ‘index child’).

Participants who agree to take part in the EMA-component then receive instruction on how to install and use the EMA app, Ethica Data [81], on their smartphone. If a participant does not have a smartphone, they can borrow one from the research team. Participants also receive a written copy of the instruction including tips for troubleshooting the app if needed.

Finally, the participant is randomized to the intervention or control condition using the Castor Electronic Data Capture randomization module [80]. Participants are directly informed of their outcome. If a participant in randomized to the intervention condition does not have a computer, laptop or tablet at home, they will be instructed on how they can use computer rooms at their treatment location to complete the online modules.

#### Week 0: first EMA-period

The first EMA-period starts the day after pretest and runs for seven days. The app stops sending questionnaires automatically after the seventh day, but should remain installed for the second EMA-period.

#### Week 1–9: intervention period and/or continuation of TAU

Eight days after pretest, participants in the intervention condition receive an e-mail giving them access to the online intervention platform. A prevention professional contacts the participant to plan the in-person sessions. The five online modules and three in-person sessions are meant to be completed at a pace of one per week. The intervention period runs for nine weeks, giving participants extra time in case there is a week in which they do not manage to complete a module or session. For all participants, TAU will continue as normal during and following participation in this study.

#### Week 10: posttest

In week 10, all participants are contacted by a research assistant to plan the posttest assessment. To improve retention rates, each participant is contacted several times by phone and e-mail if the initial contact attempt is unsuccessful. Depending on their preference, participants can complete the questionnaires with support from a researcher on video call or at their treatment location.

#### Week 10: second EMA-period

The day after posttest, the second EMA-period starts. Measures and procedure are identical to the first EMA-period.

#### Week 22: follow-up

In week 22, all participants are contacted by a research assistant to plan an appointment for the follow-up assessment. The procedure is identical to that at posttest. After completing the questionnaires, control condition participants receive an e-mail inviting them to the online KopOpOuders-PTSD modules and highlighting parenting support options at Arkin. Figure 1 depicts an overview of the procedure.

**Fig. 1 Fig1:**
[figure not shown]
Flowchart of Study Procedure. Note. ^a^ The intervention period has a one-week margin in case there is a week in which the participant cannot participate (“Break”); in the figure, the break is in week 4, but this may vary according to participant preference

#### Adherence and compliance monitoring

To accurately interpret intervention effects, documenting treatment adherence and compliance in participants and prevention professionals is important. Participants’ adherence is monitored in three ways: completion of online modules and use of PTSD-specific content in the online library (monitored automatically by the intervention platform software), and attendance of in-person sessions (recorded by the prevention professional leading the sessions). In prevention professionals, implementation fidelity is promoted and monitored through mandatory training and monthly intervision sessions with the research team. In each intervision session, a research team member will capture factors affecting intervention fidelity through implementation logs. These implementation logs will be used to identify where guidance and feedback is needed in the intervision sessions. Furthermore, they will be thematically analyzed and described in an implementation report after completion of the study.

### Instruments

#### Primary outcomes

##### Macro-level: parenting behavior

Parenting behavior is measured using the Dutch translation of the caregiver-reported Alabama Parenting Questionnaire (APQ [86, 87]). The APQ is a 42-item questionnaire with five subscales: positive involvement with children, supervision/monitoring, use of positive discipline techniques, consistency in discipline techniques, and use of corporal punishment. Items describe parenting behaviors and situations (e.g., ‘You don’t tell your child where you are going’), which are scored for frequency on a five-point Likert scale ranging from ‘never’ (1) to ‘always’ (5). APQ total scores range from 42 to 210. However, subscales are often analyzed separately, with higher scores reflecting higher parenting skills on the ‘positive involvement’ and ‘positive discipline techniques’ subscales, and lower parenting skills on the other three subscales. In this study, we will use the total score as the primary outcome for the main analysis (research question 1) and perform additional analyses on the separate subscales. The APQ has good psychometric properties, with adequate to good internal consistency [88, 89] good test-retest reliability [90] and good construct validity [88, 89].

##### Micro-level: real-time parenting behavior

When participants report being currently or recently in contact with the index child in the EMA questionnaire, parenting behavior is assessed using eight adapted items from the Parenting Behavior Inventory (PBI [91]). The Dutch translation of the PBI was obtained from Visser and colleagues [92]. The PBI contains 20 items which comprise two independent subscales: hostile/coercive and supportive/engaged. Items describe parenting behaviors, which parents rate for frequency on a seven-point Likert scale ranging from ‘Never’ (1) to ‘Always’ (7). The PBI has good psychometric properties, with excellent internal consistency for both independent subscales, adequate to good content validity, and good test-retest reliability [91]. We have selected eight PBI items, of which four from each subscale. The wording of these items has been changed slightly to fit with the EMA format (e.g., ‘I say mean things to my child that could make them feel bad’ becomes ‘This morning… I have said mean things to my child that could make them feel bad’). We have also changed the response scale to a three-point Likert scale: ‘Not true’ (1), ‘Somewhat true’ (2), ‘Certainly true’ (3). Scores on each of the two subscales range from 4 to 12. The total score of the two subscales combined ranges from 8 to 24. This total score will be used to test intervention effects (research question 2). For this study, we will call this questionnaire the ‘Short Parenting Scale for EMA’ (SPS-EMA). Because this novel adaptation of the PBI has not previously been used in EMA, we tested the SPS-EMA in a small-scale pilot study. We found the items to have sufficient frequency and variability for use with EMA.

#### Secondary endpoints

##### Macro-level: perceived parenting competence

Perceived parenting competence is measured using the Dutch translation of the Parenting Sense of Competence Scale (PSOCS [93]). The PSOCS is a 16-item questionnaire comprising two subscales: satisfaction and efficacy. We will use the total score for the main analysis (research question 3) and perform additional analyses on the two subscales. Items are posed as statements (e.g., ‘Being a parent makes me tense and anxious’), which are scored on a six-point Likert scale ranging from ‘strongly disagree’ (1) to ‘strongly agree (6). PSOCS total scores range from 16 to 96. The PSOCS has adequate to excellent internal consistency, good test-retest reliability, and good construct validity [93–95].

